### Ethical Considerations

The Mayo Foundation Institutional Review Board served as the reliant international review board (IRB) of record for all participating institutions including Mayo Clinic, the University of Michigan, Yale University, and the University of Minnesota. Written informed consent, using a mobile platform, was obtained from all study participants before study participation. Use of the mobile platform to obtain informed consent and collect study outcomes was IRB approved (#18-010484). All patient-related research information was deidentified before data analysis. All patients were remunerated US $50 for the initial screening, US $150 for the first clinical assessment, and US $100 for the second clinical assessment.

### Reporting Guidelines

The reporting of study methods and results adhered to the Strengthening the Reporting of Observational Studies in Epidemiology (STROBE) guidelines [66].

## Results

### Study Recruitment

#### Overview

The research proposal was funded on January 3, 2019, and patient recruitment began on August 1, 2019. However, due to the COVID-19 pandemic, patient recruitment was slowed in March 2020 and halted in April 2020 for a 4-month period. Over the next 2-year period, patient recruitment was slowed or interrupted at each clinical site based on the regional impact and the individual health care system response to the COVID-19 pandemic. Compared with the more urban setting of the University of Michigan and Yale University, the impact of COVID-19 pandemic on the rural catchment area of Mayo Clinic was less disruptive and associated with fewer interruptions. As a result, the majority of patient and clinician recruitment occurred at the Mayo Clinic site. Due to the unanticipated effects of the COVID-19 pandemic on clinical research activities, two 6-month, no-cost extensions were granted by the funding agency, and all recruitment and data collection were completed by August 2024.

#### Patient Recruitment

Table 1 depicts the total number of cases and controls recruited at each site. The Mayo Clinic site recruited 83% (855/1030) of the cohort, the Yale University site recruited 14.3% (147/1030), and the University of Michigan site recruited 2.7% (28/1030). Data analysis of patient characteristics associated with UPOU has been completed and the manuscript is under active development.

**Table 1 table1:** Patient recruitment by study site.

Study site	Patients, n (%)		
	Total (n=1030)	Cases (n=513)	Controls (n=517)
Mayo Clinic	855 (83)	422 (82.3)	433 (83.8)
University of Michigan	28 (2.7)	15 (2.9)	13 (2.5)
Yale University	147 (14.3)	76 (14.8)	71 (13.7)

#### Clinician Recruitment

A total of 148 clinicians completed the CAOS survey. The Mayo Clinic site recruited 146 (98.6%) clinicians, and 2 (1.4%) clinicians were recruited at the University of Michigan site. Recruitment of unique clinicians at the Mayo Clinic site was limited, in part, by clinicians who prescribed opioids to more than 1 patient. Due to unanticipated administrative barriers at Yale University, no clinicians were recruited at this site. The data analysis of clinician characteristics associated with UPOU has been completed and the manuscript is under active development.

#### SEMs and National Administrative Claims Database Analysis

The SEMs are under active development, and the results of the SEMs based on the case-control data will be submitted for publication in a peer-review journal. The administrative claims database from OLDW has been successfully retrieved and is actively being prepared for data analysis using the SEMs developed from the case-control data. The results of the SEM and OLDW analysis will be submitted for publication in a peer-review journal.

## Discussion

### Principal Findings

The anticipated results of this prospective, case-control study should provide ample data to understand how patient, clinician, and practice environment characteristics facilitate or impede development of UPOU. More specifically, multivariate logistic regression models will elucidate the individual influence of each domain (eg, patient, clinician, and practice environment) on UPOU and multilevel SEMs will provide an estimate of latent variables and test associations at and across these different levels for categorical and continuous outcomes. Widespread dissemination will be facilitated by the results derived from the broader analysis of the OLDW.

The results of this study will further build existing knowledge about the clinical characteristics associated with UPOU. For example, in a systematic review and meta-analysis of 33 studies comprised of 1,922,743 individuals, patient-level characteristics associated with UPOU after surgery included female sex; high school level education; previous mental health diagnosis of depression, anxiety, or posttraumatic stress disorder; cocaine or alcohol use disorder; tobacco use; and preoperative use of prescription opioids, antidepressants, benzodiazepines, or antipsychotic medications [67]. In addition, a history of back and neck pain, fibromyalgia, and migraine headache were associated with UPOU after surgery [67]. However, interpretation of these findings was limited by varying definitions opioid naivety and UPOU, clinical and statistical heterogeneity, and varying approaches for establishing baseline clinical characteristics. The imprecision of the meta-analysis was due, in part, to the use of large administrative and insurance claims data by studies included in the systematic review, which limited the number of studies that were available for inclusion in the subgroup analysis of patient characteristics. The results of our study will extend these findings by including surgical and nonsurgical patients and using uniform definitions of opioid naivety and UPOU. Finally, due to imprecision associated with establishing previous psychiatric diagnoses [68,69], the severity of current depressive symptoms, the presence of positive and negative affect, and the level of pain catastrophizing were included as study outcomes.

The clinical and research implications of the study results are important for 2 reasons. First, this study leveraged a conceptual framework and a case-control design to identify patient and clinician characteristics associated with UPOU. It is anticipated that the patient characteristics will have an immediate and significant impact on the clinical care of opioid-naive adults receiving appropriately indicated opioid prescriptions for short-term use. The identified clinician characteristics will provide the opportunity to develop and deliver targeted educational content to clinicians to raise awareness of UPOU. Second, development of SEMs and secondary testing in the much larger and more diverse cohort derived from the OLDW will facilitate the design of future research projects aimed at reducing development of UPOU.

### Limitations

The timeline of the research project was disrupted by the COVID-19 pandemic, but data collection was facilitated by no-cost extensions and leveraging the rural catchment area of Mayo Clinic. This produced an imbalance in the number of patients and clinicians recruited between the 3 clinical sites. While the overall target sample size was largely attained and therefore target statistical power was met, the imbalance potentially limited generalizability and precludes site-specific analyses for Yale University and University of Michigan. The opioid use status of cases and controls were based on the number of prescriptions issued by clinicians. As a result, discrepancies could exist between the number of prescriptions issued compared with the number of prescriptions dispensed by pharmacies. Finally, the CONSORT criteria were adapted to categorize opioid use 3 months following the initial prescription. Although it is possible that the status of opioid use could change over time, all patients were followed an additional 6 months to assess the stability of the opioid use category in cases and controls.

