#### Sample Size Estimates

Based on our preliminary work [3,9,57-62], we estimated the rate of episodic opioid use would be 20% and the estimated rate of long-term use would be 7%. This would yield approximately 200 (780 × .27 = 210.6) patients developing some form of UPOU at each site. The analysis for specific aim 1 involved examining a wide variety of predictors of UPOU rather than 1 specific exposure. As a result, the minimum detectable odds ratios across a range of sample sizes were calculated. Setting the power at 0.8 and α at .05 (2-tailed), a total sample size of 1200 (600 cases and 600 controls) allowed detection of an odds ratio of 1.38 with a predictor that had a prevalence of 0.5 in controls and zero correlation in exposure between cases and controls. The detectable odds ratio (OR) goes up as the correlation between cases and controls becomes positive (detectable OR=1.48 with *r*=0.3), and it also increases as the prevalence of the exposure in the control group increases (detectable OR=1.55 with *r*=0.3 and prevalence of exposure=0.7 in controls).

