#### Sample Size Estimates

There was no information available to predict how many unique clinicians prescribe opioids to patients in aim 1. A 2013 meta-analysis of provider surveys estimated a survey response rate among health professionals of 53% [63]. Thus, we conservatively estimated the response rate would be between 35% to 65% and anticipated between 410 and 760 clinicians would complete the survey.

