#### Sample Size Estimates

Common algorithms do not exist for assessing power for complex SEM; however, 3 aspects of sample size were considered. First, because of the iterative and complex nature of SEMs, it was important to verify that the sample size was sufficiently large to produce stable model estimates. There are simulation studies suggesting that for models of the size and complexity proposed, minimum sample sizes for model stability would likely be in the hundreds [64]. Second, comparing models requires a certain sample size. Published estimates of model degrees of freedom suggest that sample sizes in the hundreds would be sufficient to discriminate competing models [64]. Finally, given a set sample size, an expected detectable effect size was estimated. Setting statistical significance at =.05 (2-sided tests) and power at 80%, a sample size of 500, for example, would allow detection effects of approximately 0.13 SD units across time (ie, considered a small effect). Even accounting for losses due to missing data, which can become an issue when combining multiple sources of data at multiple levels, the proposed sample size of 1200 patients, and the smaller number of clinician and practice environments in which they were nested, should be sufficient to estimate stable, comprehensive models and detect relatively small associations between constructs.

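### The Limitations section says target power was met, but 513 cases and 517 controls give about 73–74% power in aim 1, and the clinician shortfall is not reported

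*Protocol article*

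**What the plan says.** All references are to the protocol article.

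- **Aim 1, Sample Size Estimates.** With power 0.8 and two-sided alpha .05, "a total sample size of 1200 (600 cases and 600 controls) allowed detection of an odds ratio of 1.38", for a predictor with control prevalence 0.5 and no case-control correlation in exposure. Two further scenarios follow: 1.48 with correlation 0.3, and 1.55 with correlation 0.3 and prevalence 0.7.
- **Results, Patient Recruitment (Table 1).** 1030 patients: 513 cases and 517 controls. "The Mayo Clinic site recruited 83% (855/1030) of the cohort".
- **Aim 2, Sample Size Estimates.** The investigators "anticipated between 410 and 760 clinicians would complete the survey". No power, alpha or effect size is given.
- **Results, Clinician Recruitment.** "A total of 148 clinicians completed the CAOS survey": 146 at Mayo Clinic, 2 at Michigan, none at Yale.
- **Aim 3, Sample Size Estimates.** As an illustration, a sample of 500 "would allow detection effects of approximately 0.13 SD units across time". The section then argues that 1200 patients, with the smaller number of clinicians and practices they are nested in, should be enough.
- **Discussion, Limitations.** "While the overall target sample size was largely attained and therefore target statistical power was met". The next clause concedes an imbalance between sites, limited generalizability, and no site-specific analyses for Yale or Michigan.

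**The concern.** The Limitations sentence infers full power from a sample that was nearly reached. That inference needs spare power in the plan, and the aim 1 plan appears to have none: the odds ratios it quotes are those that 600 pairs just detect at 80%. A shortfall of about 14% in patients must then bring power below the target.

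The sentence also speaks of an overall target without separating the aims. Clinicians appear in that section only as part of the site imbalance, never as a count far below what was anticipated.

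The article says the aim 1 and aim 2 analyses are complete, with manuscripts in development. A statement that target power was met could be carried into those reports and used to treat null associations as adequately powered negatives. The risk is greatest for clinician and practice characteristics.

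**Working it through.** **Inputs.** Power 0.80, two-sided alpha 0.05, 600 pairs, and three scenarios of control prevalence p0, exposure correlation r and odds ratio (aim 1, Sample Size Estimates). Matching is 1:1 on initial issue date within 2 weeks (timeline section), and the analysis is McNemar and conditional logistic regression (aim 1, Data Analysis Plan). Attained: 513 cases, 517 controls, 148 clinicians (Results).

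**Formula.** Let p1 be the exposure prevalence in cases and s = r·√[p1(1−p1)p0(1−p0)]. The discordant-pair probabilities are

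- a = p1(1−p0) − s (case exposed, control not)
- b = p0(1−p1) − s (control exposed, case not)

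with p1 solved so that a/b equals the odds ratio. With d = a − b, t = a + b and n pairs,

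power = Φ{ [d√n − 1.96√t] / √(t − d²) }.

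**Step 1: reproduce the plan at 600 pairs.** For OR 1.38, p0 = 0.5, r = 0: p1 = 0.5798, a = 0.2899, b = 0.2101, d = 0.0798, t = 0.5000. Then (0.0798·√600 − 1.96·√0.5)/0.7026 = (1.955 − 1.386)/0.7026 = 0.811, so power is 79.1%.

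**Step 2: repeat at 513 pairs.** There cannot be more 1:1 pairs than cases. For the same scenario, (1.808 − 1.386)/0.7026 = 0.601, so power is 72.6%.

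| Scenario | Power, 600 pairs | Detectable OR, 600 pairs | Power, 513 pairs | Detectable OR, 513 pairs |
|---|---|---|---|---|
| OR 1.38, p0 0.5, r 0 | 79.1% | 1.385 | 72.6% | 1.42 |
| OR 1.48, p0 0.5, r 0.3 | 80.4% | 1.477 | 74.0% | 1.53 |
| OR 1.55, p0 0.7, r 0.3 | 79.8% | 1.552 | 73.3% | 1.61 |

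The plan's three odds ratios are reproduced, so the method is a fair yardstick. Other normal approximations move these results only slightly (the second detectable odds ratio lies at 1.52 to 1.53, the third power at 73 to 74%). An unmatched comparison of 513 with 517 at OR 1.38 gives 73.0%.

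**Step 3: share of the patient target.** 513/600 = 85.5%, 517/600 = 86.2%, 1030/1200 = 85.8%.

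**Step 4: clinicians.** 148/410 = 36.1% and 148/760 = 19.5%. One site supplied 146/148 = 98.6%. No aim 2 power can be recomputed, because none is stated.

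**Step 5: the aim 3 illustration.** (1.960 + 0.842)/√500 = 0.125 SD, which agrees with the stated 0.13 as a one-sample or within-person effect. A comparison of two groups of 250 would need 2 × 2.802/√500 = 0.25 SD, so the stated figure is not a between-group one. On its own terms, 1030 patients detect 2.802/√1030 = 0.087 SD, and 0.13 SD has 98.7% power.

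**The case against.** **The aim 1 effect is modest.** The plan names no single exposure and presents detectable odds ratios for illustrative scenarios, so 1.38 is not a target effect. Moving from 1.38 to 1.42 changes little in practice, and odds ratios with confidence intervals will be reported. All of this stands, and it limits the weight of the point. It does not make the sentence true: power at the planned odds ratios is 6 to 7 points below what the plan computes.

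**Much is already disclosed.** The Results give every count, and the Limitations admit the site imbalance. That is correct. What is absent is any comparison of 148 clinicians with the 410 to 760 anticipated.

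**Stronger readings the documents do not support.**

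- *Stated power was missed in every aim.* Aim 2 states none; 410 to 760 is an expected number of respondents, and the section says there was no information to predict the number of unique prescribers. The aim 3 illustration is still exceeded at patient level.
- *Only 506 pairs exist* (422 + 13 + 71, if pairs lie within site). The article specifies matching by date only, and its conditional models include a site effect, which within-site pairs could not inform. If pairing was within site, power would be about 72 to 73%, and the conclusion would be the same.
- *148 clinicians can be treated as two independent groups to give a detectable difference.* Aim 2 regresses patient-level outcome on clinician characteristics, and some clinicians prescribed to several patients. Precision depends on linkage and clustering that the article does not report.
- *The two-group figure of 0.25 SD is the true aim 3 power.* It is not multilevel structural equation power either. It shows only which contrast the 0.13 SD describes.

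**Conclusion.** The point holds for aim 1. By the article's own planning figures, attained power is about 73% at OR 1.38, 74% at OR 1.48 and 73 to 74% at OR 1.55, not 80%. This assumes the plan's stated prevalences and correlations and that every case has a matched control. Fewer complete pairs would lower power further.

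For aim 2 the finding is an unreported shortfall in sample size, to 36% of the lower anticipated figure and nearly all from one site. It is not a missed power target. For aim 3, the patient-level illustration survives on its own terms, but the article gives no power figure for clinician or cross-level effects. Nothing in it therefore supports a claim of adequate power at those levels.

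No planned analysis is invalidated. The error is in a factual statement that guides how null results will be read.

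**What to change.** Replace the Limitations sentence with a statement that:

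1. 86% of the patient target was reached (1030 of 1200).
2. Aim 1 power at the planned odds ratios is about 73 to 74%; alternatively, the odds ratios detectable with 80% power are about 1.42, 1.52 to 1.53 and 1.61 in the three planned scenarios.
3. 148 clinicians responded against 410 to 760 anticipated, essentially from one site and with none from Yale, so null clinician and practice findings in aims 2 and 3 cannot be read as adequately powered negatives.

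If the 0.13 SD illustration is kept in the aim 3 section, add that it refers to a within-person or one-sample effect and not to the case-control contrast.

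This costs a few sentences. No data collection or analysis changes, and the stated figures become slightly less favourable. The aim 1 and aim 2 manuscripts should carry the same wording.

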### Conclusions

Following completion of data analysis, the study results will be immediately available for widespread dissemination in clinical practice and for use in ongoing research projects. It is anticipated that EHR systems will be leveraged to identify at risk patients receiving an initial opioid prescription and to send alert messages to members of the care team. This preemptive approach could also be used to develop direct-to-patient educational materials to raise awareness of the risk factors for developing UPOU.

## Abbreviations

AOS: Analgesic Outcomes Study
ASSIST: Alcohol, Smoking, and Substance Involvement Screening Test
CAOS: Clinicians’ Attitudes and Beliefs About Opioids Survey
CONSORT: Consortium to Study Opioid Risks and Trends
CTSA: Clinical and Translational Science Awards
EHR: electronic health record
FDA: Food and Drug Administration
ICD: International Classification of Diseases
IRB: institutional review board
MAR: missing at random
MBM: Michigan Body Map
MCAR: missing completely at random
MPI: Multidimensional Pain Inventory
NIH: National Institutes of Health
OLDW: OptumLabs Data Warehouse
OR: odds ratio
REP: Rochester Epidemiology Project
SEM: structural equation modeling
STROBE: Strengthening the Reporting of Observational Studies in Epidemiology
UPOU: unintended prolonged opioid use
